### Study intervention

#### Experimental intervention group

All training sessions will take place in a publicly available fitness center in Cologne, Germany. Participants of the intervention group will conduct three training sessions per week for a period of 12 weeks. In groups of maximal ten, the participants will perform endurance and resistance exercises for 60 min with 30 min of resistance exercises and 20 min of endurance/ strength endurance exercises. Each session will be supervised by MS experienced exercise scientists. To guarantee appropriate muscle activation, a 10-min warm-up with light aerobic activity and mobilization will be applied. An additional table shows the exercise program in more detail (see Additional file 1). To avoid difficulties with fixed-time training sessions and to improve adherence, participants will be able to choose between different weekdays and time slots.

A progressive periodization with step by step learning will be applied during the first 2 weeks of the intervention to guarantee precise movement execution of free weight resistance exercises. Thereafter, the participants will increase the load in consultation with the trainer.

The endurance / strength-endurance part comprises alternating short ergometer exercises, body weight exercises and exercises with small, functional devices (e.g. medicine ball or kettlebell) with rest periods of at least 1 min after each exercise. The exercises follow the principle “as much repetitions as possible”. The workload will be increased from 4 × 2 min to 4 × 3 min to 4 × 4 min according to the performance level of the participants.

#### Passive control group

For ethical reasons, it is not justifiable to withhold the exercise intervention completely from the passive control group. Therefore, the study controls will be included in a waiting list to get offered the same exercise program after T_2_ (Fig. 1).

**Fig. 1 Fig1:**
[figure not shown]
Flow diagram of this study. Baseline testing (T_0_) will be done before stratified randomization/allocation to either group. There will be a further collection of blood samples 6 weeks after intervention onset (midpoint) at rest (T_1_), after resistance exercises (T_1.1_) and immediately after the training session (T_1.2_) to investigate effects of acute training. Assessment of blood samples from the control group at T_1_ will be done at the German Sport University Cologne without further measurements at T_1.1_ and T_1.2_. After the 12-week intervention period (T_2_), all outcome measures will be assessed 48 h after the last training session to investigate effects of chronic training

### Outcomes and assessments

#### Primary outcome

The primary aim of this study will be to examine the effect of a 12-week exercise intervention period on serum concentrations of MMP-2 compared to control (see Fig. 2). We hypothesize that the decrease in MMP-2 will be greater in exercising MS patients compared with control.

**Fig. 2 Fig2:**
[figure not shown]
Spirit diagram depicting the schedule of enrolment, interventions and assessments. T_0_ = baseline assessment before stratified randomization; T_1_ = collection of blood samples immediately before a training session at midpoint (6 weeks after intervention onset). Biomarkers at T_1_ will be further used for midpoint follow-up. Blood samples from the control group will be assessed at the German Sport University Cologne without further measurements at T_1.1_ and T_1.2_; T_1.1_ = collection of blood samples after resistance exercises; T_1.2_ = collection of blood samples immediately after the training session; T_2_ = assessment of outcomes 48 h after the last exercise session; * primary outcome; ** stratification factors: i) Bioimpedance analysis using lean body mass; ii) Cardiovascular fitness using Watt_max_; iii) Muscular strength using h1RM_sum_

Blood samples will be taken by qualified technicians via vein puncture from the antecubital vein in supine position at T_0_ and T_2_ at the German Sport University Cologne. Blood samples will be centrifuged at 3000 g for 10 min at 4 °C, and the supernatant will be stored at − 40 °C until study completion. MMP-2 will be determined by enzyme-linked immune sorbent assay (ELISA) (R&D Systems, Inc., Minneapolis, MN, USA) according to the manufacturer’s instructions.

#### Secondary outcomes

Blood samples to determine chronic (T_0_ to T_2_) and acute (T_1_,T_1.1_,T_1.2_) changes of biological secondary outcomes, i.e. immune cell subsets and soluble (anti-) inflammatory factors, will be collected at the same time as those of the primary outcome (see Fig. 2). Serum will be stored at − 80 °C until analysis after study completion. The assessment of physical and cognitive performance, patient-reported outcomes, body composition and biomechanical motion analysis will be done at T_0_ and T_2_.

### Immune cell counts

Numbers and proportions of T cells (CD3^+^), T-helper cells (CD3^+^CD4^+^), Th17 cells (CD3^+^CD4^+^CD161^+^CCR6^+^), and regulatory T cells (CD3^+^CD4^+^CD25^+^CD127^dim^) will be assessed at all time points (chronic (T_0_,T_2_) and acute (T_1_,T_1.1_,T_1.2_)) and determined by using flow cytometry.

Gating strategies will be applied as reported by Zimmer et al. and Wenning et al. [33, 34].

### Soluble factors

Inflammatory (MMP-9, Tumor necrosis factor-alpha (TNFα), Interferon gamma (IFNγ), Interleukin (IL)-6, IL-17) and anti-inflammatory (IL-10) soluble factors as well as TRP and metabolites (KYN, KYNA, QUIN, NAD+) will be assessed at all time points. Serum MMP-2 will be assessed at T_1_, T_1.1_ and T_1.2_ as well for investigating acute serum changes after a single training session.

Serum levels of TRP, KYN, TNFα, IFNγ, IL-6, MMP-9, IL-10 and IL-17 will be determined by using ELISA according to manufactures instructions. Levels of KYNA and QUIN will be assessed by high-performance liquid chromatography. Further, enzymes involved into the TRP degradation pathway and KYN metabolism (Kynurenin-3-Monooxygenase, Indolamin-2,3-Dioxygenase, Kynurenin-Aminotransferase) will be measured by real-time quantitative PCR.

Serum levels of neurofilament light chain (NfL) will be measured by the single-molecule enzyme-linked immunosorbent assay (ELISA) called single molecule array (Simoa). That technology was shown to be 126- and 25-fold more sensitive than regular ELISA or electrochemiluminescence, respectively [35]. Measurement will be done as described previously by Disanto et al. [36].

### Assessment of physical capacity

To assess body composition of the participants, bioelectrical impedance analysis will be used and recorded according to the manufacturer’s instructions. The calculated lean body mass will be used as a stratification factor for randomization, since visceral adipose tissue has been described to play a significant role in inflammatory signalling [37] and therefore, may impact biological outcome measures.

Cardiorespiratory fitness will be assessed on a cycle ergometer (Ergoline®, Bitz, Germany) with a progressive cardiopulmonary exercise test (CPET). Participants will begin the test at an initial intensity of 30 W (one-minute warm-up), increasing by 15 W every minute until volitional exhaustion. This will be followed by a three-minute cool-down. The resulting Watt_max_ at T_0_ will be used as a stratification factor for randomization. The individual cardiorespiratory fitness level will be monitored by direct and continuous measurements (breath by breath) of VO_2peak_ by ergospirometry (Cortex, MetaLyzer 3B-R2, Germany). Blood lactate will be measured before, immediately after and 3 min after the CPET via earlobe prick.

To assess muscular strength, a five-repetition maximum (5RM) test will be conducted for lower (leg press) and upper body compartments (chest press, lat pulldown). The American College of Sports Medicine (ACSM) guidelines will be applied to assess the 5RM [38]. These guidelines state that, firstly, the participants should warm up by completing several submaximal repetitions. Secondly, the 5RM will be determined within four trials with rest periods of 3 min between trials. Thirdly, an initial weight that is within the subject’s perceived capacity (~ 50–70% of capacity) will be chosen. Thereafter, the resistance will be progressively increased by 2.5-20 kg until the subject is not able to complete the selected repetition(s). All repetitions should be performed at the same speed of movement and range of motion to ensure consistency between trials. Lastly, the final weight lifted successfully as the absolute 5RM will be recorded.

The rest periods between training sets will be decreased to 2 min according to Miller [39] and Brown [40]. Following instructions from Landers et al. [41], the hypothetical one-repetition maximum (h1RM) will be calculated from the 5RM test results. The calculated h1RM of the different exercises are added together with the sum representing the outcome measure (h1RM_sum_) for muscular strength and will be used as a stratification factor.

### Motion capture

As maintenance of safe locomotion is important in the course of MS, a biomechanical motion analysis using a Vicon System (Vicon, Oxford, UK) and three-dimensional force plates (Kistler, Winterthur, Schweiz) will be applied. By using an inverse-dynamic model the mechanical power on the ankle as well as the absorption and the release of energy will be captured as parameters in addition to the ground reaction forces.

### Assessment of cognitive performance

To test the cognitive performance of the participants, the Brief International Cognitive Assessment for Multiple Sclerosis (BICAMS) battery [42] will be applied. The battery comprises three tests to assess information processing speed, verbal memory and visual memory which all constitute major cognitive domains affected in the course of MS.

Information processing speed will be measured with the Symbol Digit Modalities Test (SDMT). Digits from one to nine are each paired with one of nine abstract symbols, with a correct assignment being visible for the participant throughout the testing. There is a pseudo-randomized sequence of a total of 110 symbols on a working sheet. After a training part of pairing ten symbols is completed, the participant responds by saying the corresponding digits of the remaining symbols as quickly as possible. The indicator of performance is the total number of correct symbol-digit pairs in 90 s.

Verbal memory will be measured with the California Verbal Learning Test (CVLT) that shows good external validity in MS [43]. The German version will be applied according to Niemann et al. [44]. The test contains two 16-items word lists (list A, list B) of which just list A will be used in this study. The list will be read out loud by the investigator. Thereafter, the participant will be asked to recall as many words as possible without any time restriction. This procedure will be repeated in five consecutive trials. The indicator of performance is the total number of words recalled during all trials.

Visual memory will be measured with the Brief Visuospatial Memory Test-Revised (BVMT-R). Six abstract geometric figures will be shown to the participant for 10 sec in three consecutive trials. After the presentation of the visual stimulus figures, the participant will be asked to draw, without any time restriction, as many recalled figures as possible in the correct location, shape and proportion. Each figure will be scored 0, 1, or 2 based on the scoring criteria. The indicator of performance is the total recall score in all three trials.

To exclude memory effects regarding verbal and visual memory, parallel versions of the CVLT and BVMT-R will be applied at T_2_.

### Patient-reported outcomes

To assess physical activity behavior, both subjective and objective measures will be applied three times (T_0_,T_1_,T_2_).

For subjective measurement, the Godin Leisure-Time Exercise Questionnaire (GLTEQ) and the activity questionnaire will be used, respectively. The GLTEQ asks for weekly frequencies of strenuous (9 points), moderate (5 points), and mild (3 points) activities with all points being multiplied by the number of weekly conductance. Reference score units are ≥24 (≙ active), 14 to 23 (≙ moderately active) and < 14 (≙ insufficiently active) [45].

The second activity questionnaire is asking for the activity of the patients during the last 1, 6 and 12 weeks using either i) boxes to provide exact time of physical activity (in hours) and exercise (in minutes) during the last week and ii) visual analogue scales ranging from “low activity” to “high activity” to assess physical activity in the last 1, 6 and 12 weeks.

For objective measurement, an actimetry sensor (ActiGraph GT9X Link) is applied to each participant for seven consecutive days in order to identify differences in rest and activity cycles. The sensor will be attached to the hip to better monitor the activity level. There will be several interesting outcome measures with moderate to vigorous physical activity (MVPA) being the main outcome measure.

Fatigue will be assessed with the two-dimensional Fatigue Scale for Motor and Cognitive functions (FSMC). The FSMC has defined cut-off scores to differentiate between mildly (≥43 sum score), moderately (≥53 sum score) and severely (≥63 sum score) fatigued patients using 20 items with ten items for each dimension [46]. The German version shows excellent test-retest reliability [47].

Depression and anxiety will be measured with the German version of the Center for Epidemiologic Studies Depression Scale (CES-D) [48, 49]. In a 20-item measure using a four-point Likert scale, the participants will be asked to rate how often they experienced symptoms associated with depression over the past one to 2 weeks.

Health-related quality of life will be evaluated with the Multiple Sclerosis International Quality of Life Questionnaire (MusiQol) by describing nine dimensions with 31 items [50]. The German version shows good test-retest reliability [51].

Sleeping quality will be assessed by the German version of the Pittsburgh Sleep Quality Index (PSQI) [52]. Participants rate their subjective sleep quality, sleep latency, sleep duration, habitual sleep efficiency, sleep disturbances, use of sleeping medication, and daytime sleepiness over the past 4 weeks.

Social integration will be assessed with the German version of a social integration index according to Bittner et al. [53]. The index contains three domains, each scored from 0 to 2 (total range of index from 0 to 6) [54]. Level I of the index includes persons who scored 0 or 1. Further levels are II (range 2–3), III (range 4–5), and IV (6). The index includes three types of ties: 1) marital status or cohabitation, 2) contacts with close friends and family, and 3) affiliation with voluntary associations. Marital status will be scored 0 if the subject is single/divorced/widowed and 2 if the subject is married/living with a partner. Regarding contacts, subjects are given a score of 0 (0–2 contacts), 1 (3–11 contacts), or 2 (≥12 contacts). The affiliation with voluntary associations be calculated by positive responses to questions on membership in any of six types of political, religious, community, sports, or professional organizations.

All questionnaire-based patient-reported outcomes will be assessed using a tablet computer (iPad, 128GB Version 2018). For this purpose, Qualtrics Research Core software will be applied.

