## Methods/design

In this study, a two-armed single-blind randomized controlled trial design will be applied. Prior to (T_0_) and 48 h after the intervention period (T_2_), an assessment of cardiovascular fitness, muscular strength, cognitive performance, gait performance and patient-reported outcomes (depression and anxiety, fatigue, quality of life, sleep quality, physical activity behavior, social integration) will be conducted. Blood samples at rest will be taken at T_0_, midpoint (T_1_) and T_2_. To investigate acute changes of BBB markers, immune homeostasis, (anti-) inflammatory factors as well as TRP metabolites, there will be an additional assessment of blood samples before (T_1_), during (T_1.1_) and after (T_1.2_) a training session with the resting values at T_1_ being further used for midpoint follow-up. Blood samples from the control group at T_1_ will be assessed without further measurements at T_1.1_ and T_1.2_. To control for the participants’ daily activity level, the participants will be asked to adhere to a 7-day actigraphic measurement on three time-points (T_0_,T_1_,T_2_).

All assessments and blood-sampling will be conducted at the German Sport University Cologne, except for the blood samples at T_1_,T_1.1_,T_1.2_ in the intervention group. This blood sampling will be done by a physician at the fitness center.

Due to the nature of the trial, participants could not be blinded to group allocation. Assessors taking outcome measures post intervention will be blinded to group allocation. The training sessions will be supervised by MS experienced exercise scientists. The trainers will not be involved in the post assessment to keep blinding.

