### Data management

In order to monitor participant adherence to the weekly training sessions, a training sheet will be implemented that will i) show whether intervention group participants took part in the planned training sessions and ii) be used to document training progression. Participants will be contacted by email or phone if they fail to take part in two consecutive training sessions.

Additionally, as a safeguard for any potential data loss, all study data will be stored in a password-protected computer device that is not connected to the internet. Additionally, training documentation data of each participant will be entered in the computer device on a weekly basis to provide fast and easy access to training adherence and training progression.

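### Activity measures at T1 and the T2 questionnaires do not separate supervised study sessions from participants' own activity, so the arm comparison partly restates allocation and attendance

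*Protocol article*

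**What the plan says.** The abstract lists physical activity behaviour among the secondary outcomes. The section Patient-reported outcomes measures it at T0, T1 and T2 in three ways:

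- **GLTEQ:** "The GLTEQ asks for weekly frequencies of strenuous (9 points), moderate (5 points), and mild (3 points) activities". A score of 24 or more is active, 14 to 23 moderately active, and below 14 insufficiently active.
- **Second activity questionnaire:** last-week entries for physical activity (hours) and exercise (minutes), plus visual analogue scales for the last 1, 6 and 12 weeks.
- **Hip-worn sensor for seven days**, "with moderate to vigorous physical activity (MVPA) being the main outcome measure".

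Methods/design presents the actigraphy as a means of controlling for the participants' "daily activity level, the participants will be asked to adhere to a 7-day actigraphic measurement on three time-points".

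The arms differ in scheduled exercise until T2. In the exercise arm, "Participants of the intervention group will conduct three training sessions per week for a period of 12 weeks". In the control arm, "the study controls will be included in a waiting list to get offered the same exercise program after" T2. By the legends of Figures 1 and 2, T1 falls six weeks after training starts and T2 is 48 h after the last session. Secondary analysis plans a baseline-adjusted between-group ANCOVA for secondary outcomes, with simple effects to see whether the groups differ at T1 and/or T2.

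**The concern.** One set of measures has two jobs. As an outcome, it should show whether the programme changed activity behaviour. As a control, it should show what participants did apart from the programme, so that an MMP-2 difference can be read against it. If study sessions are counted, the intervention enters its own outcome in one arm only. A higher score in the exercise arm may then mean no more than that people attended.

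The second job suffers more. A participant who drops private exercise because of the study sessions may show no change, or even a rise, in the total. That compensation is one of the things a check on daily activity should detect.

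**Working it through.** There is no figure in the plan to reproduce. The check is whether the time windows overlap, and how much the sessions can contribute.

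**1. Overlap of each measure with supervised training (exercise arm only)**

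| Measure | T1 (week 6) | T2 (48 h after last session) |
|---|---|---|
| Actigraphy, 7 days | Within the training period, whether worn just before or just after T1 | Not determined |
| GLTEQ, weekly frequency | Training week | Last week, mostly training |
| Recall of 1 and 6 weeks | Training weeks | Almost entirely training |
| Recall of 12 weeks | About half training | Almost entirely training |

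Seven days of wear cannot fit into the 48 h between the last session and T2. Worn before the visit, the record includes training, up to about three sessions. Worn after it, the exercise arm has no scheduled session, but controls may begin the programme they are offered. The article does not say which applies.

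**2. Booked session time**

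Inputs, from Experimental intervention group: "the participants will perform endurance and resistance exercises for 60 min with 30 min of resistance exercises and 20 min of endurance/ strength endurance exercises", and "a 10-min warm-up with light aerobic activity and mobilization will be applied".

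- Session length: 10 + 30 + 20 = 60 min, so the stated parts add up.
- Per week: 3 × 60 = 180 min. Without warm-up: 3 × 50 = 150 min.
- At assumed attendance of 80% and 60%: 144 and 108 min (120 and 90 without warm-up).
- Control arm: 0.

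These are ceilings for MVPA. The warm-up is light, there are rest periods, and the article does not say how much of the resistance work a hip sensor would register. The stated endurance workload alone is 4 × 2 to 4 × 4 min, or 8 to 16 min per session and 24 to 48 min per week.

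**3. GLTEQ points from study sessions alone** (sessions per week × weight × attendance)

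| Rated as | 100% | 80% (assumed) | 60% (assumed) |
|---|---|---|---|
| Strenuous (9) | 27 | 21.6 | 16.2 |
| Moderate (5) | 15 | 12 | 9 |
| Mild (3) | 9 | 7.2 | 5.4 |

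At full attendance, a strenuous rating alone passes the cut-off of 24 and a moderate rating alone passes 14. A mild rating passes neither.

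**4. What a total can show**

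Write the arm difference in total activity as D = S + (own activity, exercise arm − own activity, control arm), where S is the session contribution. Only the bracket describes activity outside the programme. If S is not measured separately, the bracket cannot be recovered from D. For example, a participant who gives up three moderate private activities (−15) and attends three sessions rated moderate (+15) shows a GLTEQ change of 0. If the sessions are rated strenuous, the change is +27 − 15 = +12, an apparent rise despite full compensation.

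**5. What can be separated afterwards**

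The training sheet will "show whether intervention group participants took part in the planned training sessions", so attendance is known. The accelerometer record could be trimmed if session clock times are kept as well. A GLTEQ total can be corrected only if one knows which intensity category the participant used for the sessions. A 6- or 12-week visual analogue scale cannot be split at all.

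**The case against.** The strongest reply is that this rests on silence. Rules for trimming accelerometer data, wear-week placement and questionnaire wording often sit in a full protocol or analysis plan, and neither is shown. That has force for the actigraphy processing. It has less force for the questionnaires: as described, they ask about all activity over periods that the stated schedule fills with training, and later processing cannot reliably undo that.

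Second, total activity including sessions is a legitimate outcome. The Background stresses how few people with MS meet the exercise guidelines, and whether a community programme raises total activity is a fair question. This stands, so total MVPA should be kept. It does not, however, measure the daily activity that Methods/design wants to control for.

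Third, some separation is already available. The second questionnaire asks for exercise apart from general physical activity, attendance is recorded, and a week with three sessions leaves days without one. So it would be wrong to say that daily activity cannot be controlled for. But the exercise entry still mixes study sessions with private exercise, and the article plans no such separation.

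A reader might also infer several stronger points that the documents do not support:

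- **That T2 MVPA is contaminated by training.** The wear week could follow the visit.
- **That extra activity in controls is hidden.** Controls have no study sessions before T2, so session counting cannot mask a rise in their own activity at T1 or in the T2 questionnaires.
- **That every inactive attender moves up a GLTEQ class.** Mild ratings give 9 points, and moderate ratings at 80% attendance give 12. Both are below 14.
- **That 180 min is added MVPA.** It is booked time.

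**Conclusion.** The point holds for actigraphy and questionnaires at T1, and for the GLTEQ and the 1-, 6- and 12-week recall at T2. Followed as written, the between-arm comparison of these measures partly restates who was allocated to train and who attended. It also does not serve the stated purpose of controlling for daily activity, because session time can mask compensation in the exercise arm.

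The session contribution is at most 180 min/week of booked time (150 without warm-up), with an unknown and probably smaller share counting as MVPA. On the GLTEQ it is 9, 15 or 27 points at full attendance, depending on how participants rate the sessions. The lower attendance figures are assumptions. The remaining difference in activity outside the sessions cannot be computed from the document. For T2 actigraphy the overlap is possible but unproven.

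The consequence is confined to a secondary outcome and to the use of activity when interpreting other results. The primary MMP-2 model adjusts for baseline values and lean body mass and has no activity term, so its estimate is unaffected. The change should be made because the questionnaire part cannot be repaired reliably after data collection.

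**What to change.** 1. In the GLTEQ and the second activity questionnaire, ask about supervised study sessions separately from all other activity.
2. Record the start and end time of each attended session on the training sheet.
3. Report two MVPA figures: MVPA per valid wear time outside study sessions, as the measure for controlling daily activity, and total MVPA including sessions, as the measure of overall activity.
4. Place the T1 and T2 wear weeks identically in both arms relative to the visit, with the T2 week ending before any wait-list training starts, and state that placement.

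The cost is one questionnaire instruction, one data-processing step and slightly less usable wear time in the exercise arm, which expressing MVPA per wear time handles.
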